### 4.2 Intention to Treat (ITT)

This population includes all randomized women. Following the intention-to-treat principle, patients will be analyzed according to the preventive treatment they were assigned to at randomization. This population is the target for the analysis of efficacy.

### 4.3 Safety

This population includes all patients who received at least a dose of IPT (or at list first half on the MQs ) and had at least one post-baseline safety assessment. Patients will be analyzed according to the preventive treatment assigned. This is the target population for the safety and tolerability analysis.

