## 4 Population of analysis

### 4.1 According to protocol (ATP)

This population includes all women who fulfill all the inclusion-exclusion criteria and took the two IPTp doses, received the LLITNs and from whom data is available for the analysis.

It will be excluded from the ATP analysis if :

- No fulfill inclusion criteria
- No data on outcome
- No two complete doses of IPTp
- Only half dose of MQs
- More than 48 hours for second dose of MQs
- Less than 4 weeks (28 days) between doses of IPT (for MQs between first half dose)
- Less tablets than specified in the protocol
- Wrong study drug medication
- Weight recorded more than 7 days after delivery
- Do not receive LLITN
- Delivery of twins
- HIV infection in pregnancy

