Continuous variables will be compared between groups and adjusted for covariates and possible confounders using ordinary least square regression. Variables will be transformed to the logarithm scale if normality is improved and result presented as Proportional Difference.

Incidence of clinical malaria, overall admissions and outpatient attendances will be estimated as the number of episodes over the time at risk. Time at risk is estimated as the time from the start of follow up (recruitment in mothers, day of birth in infants) until the end of follow-up (visit one month after

[figure not shown]

Figure 2: Rules for Superiority

delivery for mothers and visit after 12 months of age in infants) or withdrawal due to censoring or death, whatever occurs first. In order to avoid to count twice the same episode of clinical malaria, subjects will not contribute to the denominator nor the numerator during an arbitrary period of 28 days after an event of clinical malaria is defined. For admissions and outpatient attendances a maximum of one episode per day will be allowed. The total number of events will be compared between groups using negative binomial regression to take into account a possible extra Poisson variation due to different frailty of the subjects. The comparison will be expressed as Relative Rate (RRate)

For the ATP cohorts, in order to allow for center differences, regression models will include site as covariate as well as season. The definition of season will be independent for each site. Interaction between site and treatment to evaluate homogeneity will be estimated using a combined test for the interaction terms. In addition of the adjusted results, the crude results for ATP cohort will be also presented.

For the efficacy, analysis will be presented for ATP and ITT populations. The analysis of ITT population are not adjusted for possible confounders. For Safety and Tolerability, analysis will be presented for Safety and ITT populations, all of them unadjusted. See section 6 for the classification of endpoints efficacy, safety or tolerability.

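### The Safety set is selected by drug received but grouped by assigned arm, so no safety table in the SAP shows events under the treatment a woman actually took

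*SAP*

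**What the plan says.** Section 4.3 sets two entry conditions for the Safety set. The first is receipt of drug: "This population includes all patients who received at least a dose of IPT", with the first half of a split MQ dose also sufficient. The second is that she "had at least one post-baseline safety assessment". The grouping rule follows: "Patients will be analyzed according to the preventive treatment assigned". The section gives the set a leading role: "This is the target population for the safety and tolerability analysis".

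Section 4.2 defines the ITT set: "This population includes all randomized women". Its grouping rule is that "patients will be analyzed according to the preventive treatment they were assigned to at randomization".

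Section 4.1 lists "Wrong study drug medication" among the reasons for exclusion from the According to Protocol (ATP) set.

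Section 5 settles which sets serve safety: "For Safety and Tolerability, analysis will be presented for Safety and ITT populations, all of them unadjusted". The headings of sections 6.4 and 6.5 name the same two sets.

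**The concern.** A safety set defined by exposure normally answers what happened to women who took a given treatment. Here exposure decides who enters, but assignment decides the column. A woman assigned to SP who is given MQ by mistake enters the Safety set because she swallowed a drug, and whatever follows is printed under SP.

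This sits badly with three other parts of the SAP:

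- Tables 16, 19 and 20 count events judged related to medication. That judgement concerns the drug taken. Under section 4.3 a reaction to MQ can appear as a drug-related event of SP.
- Section 5 counts any vomiting within 60 minutes of a dose as related, without further judgement. A wrong-drug dose would then place that reaction in the wrong column of Table 21 automatically.
- Section 3 makes the comparison of tolerability between the full-dose and split-dose MQ regimens an aim of the trial. Giving one regimen in place of the other blurs that comparison directly.

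On average, misplacement between two columns pulls them together. In a safety comparison that is the direction that understates a difference.

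**Working it through.** **No figure to reproduce.** The SAP gives no wrong-drug rate, no expected event rates and no number of women left undosed or unassessed. The check is therefore a comparison of the text, followed by arithmetic on assumed inputs.

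**1. The sets side by side**

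| Set | Who enters | Grouped by | Used for safety and tolerability |
|---|---|---|---|
| ITT (4.2) | All randomised women | Assigned arm | Yes |
| Safety (4.3) | At least one dose (or first split half) and one post-baseline safety assessment | Assigned arm | Yes |
| ATP (4.1) | Wrong-drug women removed | Not used here | No, efficacy only |

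ITT and Safety differ only by women with no dose or no post-baseline safety assessment. The set that deals with wrong-drug women is not used for safety. Sections 6.4, 6.5 and 7 contain no table grouped by drug received and no listing of discordant women.

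**2. One-way error: a share f of the SP arm receives MQ**

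Assumed vomiting risks: 30% on MQ, 7% on SP. Observed SP risk = (1 − f) × 0.07 + f × 0.30.

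- f = 1%: 0.0693 + 0.0030 = 0.0723, or 7.2%
- f = 3%: 0.0679 + 0.0090 = 0.0769, or 7.7%
- f = 5%: 0.0665 + 0.0150 = 0.0815, or 8.2%

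**3. Two-way error: a share m of each of two arms receives the other arm's treatment**

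Observed risk = (1 − m) × own risk + m × other risk, so the observed difference is (1 − 2m) times the true difference. This form also covers a swap between the two MQ regimens.

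| m | Assumed 30% vs 10%: difference (points) | RR (true 3.00) | Assumed 20% vs 10%: difference (points) | RR (true 2.00) |
|---|---|---|---|---|
| 0.5% | 19.8 | 2.96 | 9.9 | 1.99 |
| 1% | 19.6 | 2.92 | 9.8 | 1.97 |
| 2% | 19.2 | 2.85 | 9.6 | 1.94 |
| 5% | 18.0 | 2.64 | 9.0 | 1.86 |

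The difference shrinks by 1% at m = 0.5% and by 10% at m = 5%.

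**4. A rare event**

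Suppose the trial has one related serious event, after MQ in a woman assigned to SP. The assigned-arm table shows MQ 0 and SP 1. A table by drug received shows MQ 1 and SP 0. Here averaging gives no protection.

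**5. What the second safety set adds**

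If a share u of randomised women falls outside the Safety set and contributes no events, the ITT percentage is (1 − u) times the Safety percentage. For an assumed Safety rate of 30%, u = 1%, 2%, 5% and 10% gives 29.7%, 29.4%, 28.5% and 27.0%. If u is equal across arms, the risk ratio is unchanged. Under these rules the two analyses differ in denominator, not in how treatment is attributed.

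**The case against.** The strongest reply is that section 4.3 states its rule plainly and contradicts nothing. Grouping by assignment keeps the randomised comparison. That benefit is real, but the ITT safety tables already deliver it, so it is no reason to give the Safety set the same grouping.

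Other parts of the reply stand and limit the point:

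- **A reader might infer that wrong-drug women exist in number.** The SAP does not say so. The exclusion in section 4.1 is a contingency with no count, and the 5% upper value used above has no basis in the document.
- **A reader might infer that the Safety set is almost a copy of ITT.** The rules match, but the overlap is not stated. Table 1 schedules the first dose at the enrolment visit, which suggests few losses. Table 3, however, has a row for withdrawals ahead of the first dose, and the requirement for a post-baseline assessment removes others. Dropping women who never took drug is a legitimate function of a safety set.
- **A reader might infer that a rare reaction would be hidden.** Section 7 plans individual listings of adverse events, serious adverse events and dosing dates, and that list is left open. Section 2.3 places pharmacovigilance in a separate document. A serious event would be visible case by case. What section 7 does not promise is that the drug received is shown beside it, so the listings reduce the problem without removing it.
- **For common events the distortion is small** at any plausible low error rate, as the arithmetic shows.

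**Conclusion.** The point holds as a flaw in a definition. The set named as the target for safety and tolerability is selected by exposure and grouped by assignment, and no table in this SAP groups events by treatment received, although wrong-drug administration is foreseen.

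Its size cannot be computed from the SAP. Under the assumed risks and error rates it is a shift of about 0.2 to 1.2 percentage points in the SP vomiting rate, or a 1% to 10% shrinkage of a risk difference. That would not overturn a comparison of common events. The weight lies in rare drug-related events, where one case changes the column, and in the contrast between the two MQ regimens.

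The conclusion covers this SAP only. Whether the separate pharmacovigilance document groups events by drug taken cannot be judged here.

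**What to change.** Change section 4.3 so that the Safety set is analysed by treatment actually received, and add these rules:

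- **Per-dose rows of Table 21:** use the drug and regimen received at that dose.
- **Tables 16 to 20 and the rows of Table 21 that combine both doses:** for women who received different drugs or regimens at the two doses, either attribute each event to the most recent treatment received before it, or show these women separately. Choose one option in advance and state the denominator that goes with it. Classifying everyone by the first dose alone would not be enough, because events after a wrong drug at the second dose would still be misplaced.
- **Women who took only the first half of a split dose:** keep them under the split-dose MQ arm.
- **Section 7:** add a listing of every woman whose received treatment differs from the assigned one, with her events.
- **ITT safety tables:** keep them unchanged as the by-assignment view.

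The cost is a short paragraph of SAP text, a derived actual-treatment variable for each dose, and one listing. The ATP exclusion already requires wrong-drug cases to be identified, so the information should be available. The downside is that the few switched women leave their randomised group, in this set only.

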## 5 Statistical methods

For the primary analysis of efficacy, the statistical analysis will follow a sequential approach. First, hypotheses of non-inferiority between the proportion of LBW in the MQ groups and the SP group will be tested assuming as equivalence a 25% reduction or greater in LBW prevalence in the MQ groups. If non-inferiority between MQ and SP is achieved, then an analysis for superiority will be conducted comparing the MQ and SP groups using a two-sided test. Given the long half life of MQ, it has been assumed that MQ efficacy to prevent LBW will be equal in the full dose and split dose groups.

Interpretation of non-inferiority is based on the confidence intervals (CI). If the upper limit of the confidence interval (CI) of the Relative Risk (RR) MQ/SP is below 1.25, (25% of the RR) the MQ arms will be considered as non-inferior compared with SP (See figure 1). In case the upper limit of the CI is above 1.25, the trial is inconclusive as the non-inferiority hypothesis can't be rejected. If both the lower limit of the CI is below 1, the MQ treatment is considered superior to SP (See figure 2).

[figure not shown]

Figure 1: Rules for Non-inferiority

No adjustment of p-values are necessary to this switch as the “delta“ has been pre-specified, and then the interpretation based on confidence intervals can support the interpretation of non-inferiority. It is acceptable to calculate the p-value associated with a superiority test and to evaluate whether this is sufficiently small to reject convincingly the hypothesis of no difference. There is no multiplicity that affect this interpretation because in statistical terms it corresponds to a simple closed test procedure (Committee for Proprietary Medicinal Products CPMP, Points to consider on switching between superiority and non-inferiority, CMP/EWP/482/99, July 2000).

Proportions will be compared between groups using fisher exact test and presented as Risk ratio (RR) or reduction of the RR ( $1 - RR * 100\%$ ) if RR lower than 1. Adjustment for covariates and possible confounder are done using binomial regression with log link, and using robust estimates of the covariance (huber method) using the method proposed by Zou (Zou G., A modified poisson regression approach to prospective studies with binary data. American Journal of Epidemiology. 2004;159(7):702-706).

Continuous variables will be compared between groups and adjusted for covariates and possible confounders using ordinary least square regression. Variables will be transformed to the logarithm scale if normality is improved and result presented as Proportional Difference.

Incidence of clinical malaria, overall admissions and outpatient attendances will be estimated as the number of episodes over the time at risk. Time at risk is estimated as the time from the start of follow up (recruitment in mothers, day of birth in infants) until the end of follow-up (visit one month after

[figure not shown]

Figure 2: Rules for Superiority

delivery for mothers and visit after 12 months of age in infants) or withdrawal due to censoring or death, whatever occurs first. In order to avoid to count twice the same episode of clinical malaria, subjects will not contribute to the denominator nor the numerator during an arbitrary period of 28 days after an event of clinical malaria is defined. For admissions and outpatient attendances a maximum of one episode per day will be allowed. The total number of events will be compared between groups using negative binomial regression to take into account a possible extra Poisson variation due to different frailty of the subjects. The comparison will be expressed as Relative Rate (RRate)

For the ATP cohorts, in order to allow for center differences, regression models will include site as covariate as well as season. The definition of season will be independent for each site. Interaction between site and treatment to evaluate homogeneity will be estimated using a combined test for the interaction terms. In addition of the adjusted results, the crude results for ATP cohort will be also presented.

For the efficacy, analysis will be presented for ATP and ITT populations. The analysis of ITT population are not adjusted for possible confounders. For Safety and Tolerability, analysis will be presented for Safety and ITT populations, all of them unadjusted. See section 6 for the classification of endpoints efficacy, safety or tolerability.

For the ITT analysis of primary endpoint, which includes all women recruited in the study, missing values for low birth weight will be imputed as follow: For those women with miscarriage, the event will be considered as failure and they will be assigned as having LBW. For those lost to follow-up or withdraw before delivery a sensitivity analysis of worse case scenario assuming all lost of follow-up and withdrawn women having a LBW, best case scenario assuming that none have LBW and worst case scenario assuming as LBW all missing values, will be presented. In case there were countries without malaria events, a sensitivity analysis not including those countries will be also presented.

The assumption that  $MQ_s$  and  $MQ_f$  have a similar effect on the LBW will be explored by inspection of the 90% confidence intervals of the comparison between  $MQ_s$  vs  $MQ_f$  in the ATP population. If the assumption of both MQ groups are similar is rejected, then comparison between  $MQ_s$  vs SP and  $MQ_f$  vs SP will be presented instead.

For the primary outcome, the weight of children born taken after delivery but before the seven days of life are transformed according to the method proposed by ... *Greenwod* (*to be completed*) to include in

A regression analysis of the weight and day after delivery

the analysis as if they were taken at birth. Maternal and new born haemoglobines from visit 3(Delivery) not taken in the date of the delivery will not be included in the analysis of these outcomes.

The gestational age will be based on the Ballard score, but in case of missing, it will be based on the gestational age calculated with the fundal height at recruitment.

For the frequency of vomiting, dizziness, prematurity, the proportion of women with those outcomes will be compared using the methods described for proportions before.

For the tolerability, only those vomiting and dizziness judged by the investigators to be related to the medication will be included in the analysis except vomiting during the first 60 minutes after a dose of IPTp that will always be considered related to medication.

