## 2 Trial 1 objectives and endpoints

### 2.1 Primary

1. Prevalence of low birth weight (LBW) newborns (<2500g).

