## 3 Study design overview

This is a randomized open-label superiority 3 arms trial to compare 2-dose MQ with two dose of SP as IPTp in the prevention of the adverse effects of malaria during pregnancy and to compare MQ tolerability of 2 different MQ administration regimens. The three arms of the study are:

1. IPTp with SP (SP)
2. IPTp with MQ given as full dose (MQf)
3. IPTp with MQ given as an split dose (MQs)

The table 1 shows the visits and procedures schedules to the mother and the table 2 shows the visits and procedures schedule to the child.

---

At visit 4, approximately one month after end of pregnancy

Table 1: Maternal visits and procedures schedule

| Study Procedures                                    | Visit 1
Enrollment | Visit 2 | Visit 3
Delivery | Visit 4
1 Month | Unscheduled
visits | Household
visits |
|-----------------------------------------------------|-----------------------|---------|---------------------|--------------------|-----------------------|---------------------|
| Inclusion/Exclusion criteria                        | X                     |         |                     |                    |                       |                     |
| Written informed consent                            | X                     |         |                     |                    |                       |                     |
| Demographics/Medical history                        | X                     |         |                     |                    |                       |                     |
| Record of concomitant medication/
Adverse events | X                     | X       | X                   | X                  | X                     |                     |
| Physical examination / Clinical                     | X                     |         |                     |                    | X                     |                     |
| Gestational Age                                     | X                     | X       | X                   |                    | X                     |                     |
| Temperature                                         |                       |         |                     | X                  | X                     |                     |
| Blood Pressure                                      |                       |         | X                   |                    | X                     |                     |

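### The non-inferiority hypothesis is worded as a 25% reduction in low birth weight but the decision rule uses RR 1.25, and every upper limit above 1.25 is called inconclusive whatever the lower limit

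*SAP*

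**What the plan says.** The primary endpoint is the prevalence of birth weight under 2500 g (SAP section 2.1), an adverse outcome. Section 5 sets out a sequence: non-inferiority of MQ to SP first, then, only if that is achieved, a two-sided superiority comparison.

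The hypothesis sentence says that the non-inferiority hypotheses "will be tested assuming as equivalence a 25% reduction or greater in LBW prevalence in the MQ groups".

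The next paragraph gives the decision rule. If the upper confidence limit of the MQ/SP relative risk "is below 1.25, (25% of the RR) the MQ arms will be considered as non-inferior compared with SP". It then adds: "In case the upper limit of the CI is above 1.25, the trial is inconclusive as the non-inferiority hypothesis can't be rejected". The lower limit appears in one rule only, the one for superiority: "If both the lower limit of the CI is below 1, the MQ treatment is considered superior to SP".

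Section 5 does not give the confidence level for this rule. The Table 9 shell, which reports the pooled MQ against SP comparison, uses 95%.

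**The concern.** The hypothesis sentence and the decision rule point in opposite directions. A 25% or greater reduction in LBW is a benefit of MQ and cannot serve as a definition of equivalence or as a non-inferiority margin. An upper limit of 1.25 on MQ/SP is a tolerated harm.

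The decision rule is also incomplete. It calls the trial inconclusive on the upper limit alone, so it does not separate an imprecise result from one that shows MQ to be worse. The superiority step does not recover the second case, because it runs only after non-inferiority has been achieved.

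This is the threshold of the first-step primary test in an open-label trial. The boundary and the list of possible conclusions should be unambiguous before anyone sees results by arm.

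**Working it through.** **Inputs from the SAP.** Adverse binary endpoint (section 2.1); ratio MQ/SP, the 25% reduction and the bound of 1.25 (section 5); 95% level (Table 9 shell). The SAP states no sample size, power or event rate, so there is no figure of its own to reproduce. Steps 1 to 4 need none.

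**Step 1: put both statements on the RR scale.**
- Hypothesis sentence: 1 − 0.25 = 0.75.
- Decision rule: 1 + 0.25 = 1.25.
- Ratio of the boundaries: 1.25 / 0.75 = 1.67.

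**Step 2: check whether turning the ratio round reconciles them.** 1/0.75 = 1.33 and 1/1.25 = 0.80. Neither equals the other boundary, so a swap of numerator and denominator does not explain the difference.

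**Step 3: check which boundary fits the sequence.** An upper limit below 0.75 is also below 1, so it would already show superiority and the second step would be redundant. With 1.25 both steps have a purpose.

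**Step 4: apply the written rule to possible intervals.**

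| CI for RR MQ/SP | What it shows | What the section 5 text concludes |
|---|---|---|
| 0.90 to 1.20 | Within margin, no difference shown | Non-inferior; also superior, if the lower-limit rule is read literally |
| 0.77 to 1.29 | Non-inferiority not shown, no difference shown | Inconclusive |
| 1.15 to 1.70 | Non-inferiority not shown, MQ worse than SP | Inconclusive |
| 1.32 to 1.94 | MQ worse by more than the margin | Inconclusive |
| 1.02 to 1.20 | Within margin, but MQ worse than SP | Non-inferior; no wording for worse |

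**Step 5: illustrate the size with assumed inputs.** These are not in the SAP: SP prevalence pS of 8%, 12% or 15%; SP group nS of 500, 1000 or 1500; pooled MQ group nM = 2 × nS.

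*Boundary in prevalence terms.* At 12% on SP, 0.12 × 0.75 = 9% against 0.12 × 1.25 = 15%. At 8% it is 6% against 10%; at 15% it is 11.25% against 18.75%.

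*Intervals.* SE(ln RR) = √[(1 − pS)/(nS·pS) + (1 − pM)/(nM·pM)]. For pS = 0.12, nS = 1000, nM = 2000 and observed RR 1.6, pM = 0.192 and SE = √(0.88/120 + 0.808/384) = 0.0972. The 95% CI is 1.6 × exp(±1.96 × 0.0972) = 1.32 to 1.94. With observed RR 1.4, pM = 0.168, SE = √(0.88/120 + 0.832/336) = 0.0990 and the CI is 1.15 to 1.70. Across the nine settings:
- Observed RR 1.4: lower limit above 1 in 8 of 9.
- Observed RR 1.6: lower limit above 1.25 in 7 of 9.
- Observed RR 1.8: lower limit 1.29 to 1.57, above 1.25 in all 9.

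In each of these the upper limit exceeds 1.25, so the text returns inconclusive.

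*Chance of meeting each boundary b.* P = Φ[(ln b − ln RR)/SE − 1.96]. For pS = 0.12, nS = 1000 and true RR 1, SE = √(0.88/120 + 0.88/240) = 0.1049. For b = 1.25, P = Φ(0.2231/0.1049 − 1.96) = 0.57. For b = 0.75, P is below 0.0001. Across the nine settings with true RR 1, P is 0.22 to 0.84 for 1.25 and at most 0.0002 for 0.75. With true RR 0.75, P is 0.74 to above 0.99 for 1.25 and 0.025 for 0.75.

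*Reach of the last row of the table.* A lower limit above 1 with an upper limit below 1.25 needs SE < ln(1.25)/(2 × 1.96) = 0.057. In the largest assumed setting the SP term alone gives √(0.85/225) = 0.061. That row therefore cannot arise in these settings; it matters only for a complete rule.

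**The case against.** The strongest reply is that section 5 has one executable rule. It bases the interpretation on the confidence interval and names the ratio, the limit and the bound. Step 3 shows that 0.75 does not fit the sequence, so most statisticians would apply 1.25. This stands. A reader might infer that the plan fixes two equally usable thresholds; the documents do not support that. What remains is a hypothesis sentence that contradicts the rule beside it.

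A reader might also infer that the plan has no way to report harm. That goes too far. The Table 9 shell prints the RR, its 95% CI and a p-value whatever the direction, so an interval of 1.30 to 1.70 would be visible. The missing element is a worded conclusion, and the one supplied is wrong for that case. Figure 1, which the text cites for the rule, is not available here and may draw an inferior case.

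Three further inferences should not be pressed:
- Saying that the non-inferiority hypothesis cannot be rejected misnames the null, which is inferiority, but it changes no decision: an upper limit above 1.25 still gives no non-inferiority claim.
- Section 3 describes the design thus: "This is a randomized open-label superiority 3 arms trial". A plan that ends in a superiority test may carry that label, so it is not shown to be an error.
- The statement that no p-value adjustment is needed rests on a closed test procedure as well as on a pre-specified delta, so the wording conflict does not by itself overturn it.

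**Conclusion.** The point holds in two parts, both resting on the words of section 5 and on no assumed figure. First, the hypothesis sentence implies RR at or below 0.75 while the operative rule uses 1.25: opposite directions, a factor of 1.67 apart, with only 1.25 compatible with the planned sequence. Second, labelling every upper limit above 1.25 inconclusive misdescribes intervals that lie wholly above 1 or wholly above 1.25.

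The second part is a wrong verbal conclusion and does not hide the data. It is qualified by the unavailable Figure 1. How often it would arise cannot be judged from the SAP; the assumed settings show only that observed RRs of about 1.4 to 1.8 would mostly trigger it. That the 25% reduction is a superiority design effect carried into the wrong sentence is plausible, but the SAP does not say so.

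Because this text governs the primary conclusion, it should be corrected before results by arm are seen.

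**What to change.** Check the protocol first: establish whether the 25% reduction is the effect size for superiority and confirm that 1.25 is the margin. Then amend section 5 as follows.

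1. State the hypothesis as H0: RR(MQ/SP) ≥ 1.25 against H1: RR(MQ/SP) < 1.25, and remove the 25% reduction from the non-inferiority sentence. If it is a design effect, move it to where the superiority objective is described.
2. Upper limit ≥ 1.25: non-inferiority not shown (H0 not rejected). Call the result inconclusive only if the lower limit is also ≤ 1.
3. Lower limit > 1: report MQ as worse than SP, alongside the non-inferiority result if the upper limit is < 1.25.
4. Lower limit > 1.25: report MQ as inferior beyond the margin.
5. Correct the superiority rule in the same paragraph so that it requires the upper limit to be below 1. As written, 0.90 to 1.20 would count as superior.
6. Check that Figures 1 and 2 show the same rules.

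The cost is SAP wording only, with no change to data collection, the analysis model or, if the protocol confirms 1.25, the margin.

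### The superiority rule is set on the wrong confidence limit, so read literally almost any non-inferior result, including no difference, counts as superiority of MQ

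*SAP*

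**What the plan says.** The primary endpoint (SAP section 2.1) is "Prevalence of low birth weight (LBW) newborns (<2500g"), an adverse outcome. Section 5 sets out a sequence.

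- **Non-inferiority.** The criterion is met "If the upper limit of the confidence interval (CI) of the Relative Risk (RR) MQ/SP is below 1.25".
- **Superiority, as a test.** Once non-inferiority is shown, "then an analysis for superiority will be conducted comparing the MQ and SP groups using a two-sided test".
- **Superiority, as an interval rule.** "If both the lower limit of the CI is below 1, the MQ treatment is considered superior to SP", with a reference to Figure 2.
- **Superiority, as a p-value.** A later paragraph allows a superiority p-value to be calculated, to "evaluate whether this is sufficiently small to reject convincingly the hypothesis of no difference". It also argues that no multiplicity adjustment is needed, because the switch is a closed testing procedure.

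The interval rule names no confidence level. The Table 9 shell, for pooled MQ against SP, shows 95%; the Table 11 shell labels its MQ against SP column 90%.

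**The concern.** With an adverse outcome and the ratio taken as MQ over SP, MQ is shown to be better only when the whole interval lies below 1, that is, when its upper limit does. The SAP puts the condition on the lower limit. An interval centred on 1 meets it, and so do many centred above 1.

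The superiority step then adds almost nothing to the non-inferiority step: a trial that has only excluded a 25% relative increase in low birth weight would be reported as showing that MQ is better. Section 3 introduces the study with the words "This is a randomized open-label superiority 3 arms trial to compare 2-dose MQ with two dose of SP", so this sentence governs its main claim. The closed-testing argument also depends on the superiority step being a valid test at its own level, and the rule as written is not one.

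**Working it through.** The SAP states no sample size, low birth weight rate, allocation ratio or alpha, so it has no figure of its own to reproduce. What can be computed is how the written rule behaves.

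**Inputs from the SAP:** relative risk MQ/SP, margin 1.25, and the 95% interval of Table 9.

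**Assumed inputs:** low birth weight on SP 5% to 20%, 500 to 3000 women on SP, and pooled MQ equal to or twice the size of SP.

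**The rules on the log scale.** Let L be the estimated log relative risk and SE its standard error, where SE² = (1−p0)/(p0·n0) + (1−p1)/(p1·n1), with 0 for SP and 1 for MQ.

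- Non-inferior: L < ln(1.25) − 1.96·SE = 0.2231 − 1.96·SE
- Superior as written (lower limit below 1): L < +1.96·SE
- Superior as normally defined (upper limit below 1): L < −1.96·SE

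**How often does non-inferior imply superior as written?** Always, when 0.2231 − 1.96·SE ≤ 1.96·SE, that is, when SE ≥ 0.2231/3.92 = 0.0569. With 2:1 pooling, a smaller SE needs more than about 8,800, 4,170, 2,620 or 1,850 women on SP at rates of 5%, 10%, 15% or 20%. Below that SE, at a true relative risk of 1, at least 97.5% of non-inferior results still meet the written rule.

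**Examples (95% intervals):**

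| MQ | SP | Relative risk (interval) | Written rule | Upper limit below 1? |
|---|---|---|---|---|
| 300/2000 | 150/1000 | 1.00 (0.83 to 1.20) | superior | no |
| 306/2000 | 150/1000 | 1.02 (0.85 to 1.22) | superior | no |
| 630/6000 | 300/3000 | 1.05 (0.92 to 1.20) | superior | no |

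For the first row, SE = √(1/300 − 1/2000 + 1/150 − 1/1000) = √0.0085 = 0.0922, and exp(±1.96 × 0.0922) gives 0.83 and 1.20.

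**Probability of declaring superiority when the true relative risk is 1.** Without the non-inferiority step, the written rule gives Φ(1.96) = 97.5% and the normal rule gives 2.5%. With the step, and SE ≥ 0.0569, the written rule gives Φ(0.2231/SE − 1.96). At 12% on SP and 2:1 pooling, SE² = 7.333 × 1.5/n:

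| Women per arm | SE | 0.2231/SE − 1.96 | Written rule (formula) | Written rule (simulation) |
|---|---|---|---|---|
| 500 | 0.148 | −0.46 | 32% | 33% |
| 1000 | 0.105 | 0.17 | 57% | 56% |
| 1500 | 0.086 | 0.65 | 74% | 73% |

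The simulation used 200,000 trials per setting; the upper-limit rule gave 2.5% to 2.7%. For rates of 10% to 15% and 500 to 1500 per arm, the simulated range under the written rule is 28% to 83%. Over the full assumed range the formula gives 12.5% to 97.5%.

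**If MQ is truly 10% worse (relative risk 1.10).** At 12% on SP and 1500 per arm, SE = √(7.333/1500 + 6.576/3000) = 0.0841. The written rule gives Φ((0.2231 − 0.0953)/0.0841 − 1.96) = Φ(−0.44) = 33%; the upper-limit rule gives about 0.1%.

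**The case against.** The strongest reply is that nobody would apply the sentence literally. It is ungrammatical, and the word *both* suggests that a mention of the upper limit was lost. Section 5 calls for a two-sided superiority test before it and discusses a superiority p-value after it, and Table 9 has a p-value column. An analyst working from the test would not call an interval of 0.83 to 1.20 superior. Figure 2, which the sentence cites, may show the right rule.

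Much of this is fair. The sentence is probably a slip, and the error rates above apply only if the interval rule is followed as written. But the p-value wording is permissive and sets no alpha, and nothing says that the test overrides the interval rule. Section 5 therefore holds two descriptions that disagree for every non-inferior interval containing 1. Figure 2 is not visible in the text reviewed. If it is right, the text contradicts it.

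It is also true that the percentages rest on assumed inputs, and that over most of the range they equal the chance of passing the 1.25 margin. In a very precise trial with a true relative risk above 1, the written rule does filter: at SE 0.03 and relative risk 1.10, only about 11% of non-inferior results meet it. None of this makes the sentence correct.

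**Conclusion.** The concern holds. The interval rule for superiority on the primary endpoint names the wrong limit, no readable text corrects it, and it conflicts with the two-sided test in the same section. Followed literally, it does not control the type I error of the superiority claim: every non-inferior result is called superior unless SE(log RR) is below 0.057. Only the size of the false-superiority rate depends on the assumed sample size, event rate and allocation. Because the sentence decides the trial's headline conclusion, it must be corrected before the analysis.

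**What to change.** Replace the sentence with, for example: *If the upper limit of the two-sided 95% confidence interval of the relative risk MQ/SP is below 1 (so that both limits are below 1), MQ is considered superior to SP.* This brings the probability of declaring superiority at a true relative risk of 1 back to about 2.5%.

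Alongside it:

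- Check that Figure 2 shows the same rule.
- State the 95% level in the rule itself, in line with Table 9, and say what the 90% MQ against SP interval in Table 11 is for.
- Say that this interval decides superiority and that the two-sided p-value supports it, so that the section holds one rule.

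The cost is one sentence of SAP wording plus these checks. No change to design, data or sample size is involved.
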